#### **8.4 Analysis of the secondary outcomes**

The change from baseline to the end of the treatment month and to the 8-week follow-up end-  
point will be analyzed using traditional end-point analysis (paired T-test) and latent growth curve  
analysis.

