## 1. Background and Rationale

Depression is one of the leading causes of morbidity and mortality worldwide, carrying massive economic, societal, and personal burdens. Treatment-resistance is a growing phenomenon, and an estimated one in three of all depressed patients will fail to respond to multiple trials of available psychotherapeutic and pharmacologic treatments. Bipolar depression, in particular, is considered to be especially difficult to treat.

Intravenous (IV) infusions of subanesthetic doses of ketamine (most commonly 0.5mg per kg bodyweight over 40 minutes) have shown significant promise for a range of psychiatric conditions, including treatment-resistant and bipolar depression – even in cases where multiple treatments including electroconvulsive therapy have failed. These benefits typically appear rapidly in responders, within hours or days of initial treatment, though may not persist.

Ketamine infusions are typically well-tolerated and exceedingly safe when employed with appropriate precautions. Nevertheless, ketamine is well-known as a dissociative anesthetic in that it engenders a temporary altered state of consciousness, which may be distressing. These so-called dissociative effects are amongst the leading causes of discontinuing treatment with ketamine. The other major short-term transient adverse effect is increase in both blood pressure and heart rate.

Indeed, it has been reported that blood pressures exceeding 180/100 mmHg and/or heart rate  $\geq 110$  beats per minute affect up to 30% of Treatment-Resistant Depression (TRD) patients receiving ketamine, and 80% of blood pressure peak elevations during ketamine infusions (0.5 mg/kg

infused over 40 minutes) occur between 30- 40 minutes after infusion onset, with a peak ketamine plasma concentration occurring at 40 minutes.

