### **2.2 Secondary objectives**

As secondary objectives, we aim to assess if music can modulate diastolic blood pressure and clinical response to repetitive sub-anesthetic IV infusions of ketamine in depression, anxiety, suicidality, sleep impairment, and psychological/physical pain.

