### 3. Study Design

This is a prospective, two-center, single-blinded, pragmatic randomized controlled trial with a parallel two-arm design to be performed in Montreal, Canada. Patients with TRD will be recruited. After completing all screening / evaluations and baseline procedures, patients will be randomized in a 1:1 ratio to receive a curated music intervention (described below), which will consist of 60 minutes of music initiated at the beginning of each infusion (intervention group) or usual care (no music; control group) during a course of six sub-anesthetic ketamine infusions. Patients who meet all inclusion criteria and none of the exclusion criteria will be entered into the study. Recruitment criteria will be intentionally permissive in order to generate results of high external validity by including clinically representative patients who may often be excluded from clinical trials. Thirty (n=30) patients are planned for enrollment in this pilot RCT. Hemodynamic evaluations will be taken at each infusion and, for the primary outcome of blood pressure, an average of the triplicate blood pressure measures by a calibrated Welch Allyn Blood Pressure Device at 0 minutes and at 40 minutes (end of infusion) will be used. Secondary outcomes will be measured at baseline and at each treatment session, as well as at 8-week follow-up. The total duration of patient participation is expected to be eight weeks including four weeks of active treatment. The total duration of the study is expected to be two years.

The study will be a two-center study performed in the Montreal area; patients will be prospectively recruited by solicitation of clinicians and by screening of ongoing referrals at the ketamine services of two academic hospitals (the Douglas Mental Health University Institute and the Jewish General Hospital) by research assistants not actively involved in their care. The

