### **4.4 Randomization Process**

Patients who successfully complete the screening assessments will be randomized into the study. Eligible patients will be 1:1 randomized to the music-intervention (intervention, n=15) or usual care (control, n=15) groups. Participants will be randomized by an independent third party affiliated with McGill University using a computer-generated randomized sequence. The randomization sequence code will stored securely for the duration of the trial. The only theoretical exception for the code to be broken will be any serious adverse event and need for subsequent participant withdrawal.

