### 384 **5.2 Secondary outcome measures (study amendment version 2.0)**

- 385 - Change in diastolic blood pressure (DBP) at 40 minutes versus at 0 minutes between  
386 intervention and control group.
- 387 - Change from baseline in mood symptoms to last treatment [ Time Frame: Baseline, Week  
388 4]
- 389 - Change from baseline in mood symptoms to Follow-up [ Time Frame: Baseline, Week 8]
- 390 - Change from baseline in anxiety symptoms to last treatment [ Time Frame: Baseline,  
391 Week 4]
- 392 - Change from baseline in anxiety symptoms to Follow-up [ Time Frame: Baseline, Week  
393 8]
- 394 - Change from baseline in suicidality symptoms to last treatment [ Time Frame: Baseline,  
395 Week 4]
- 396 - Change from baseline in suicidality symptoms to Follow-up [ Time Frame: Baseline,  
397 Week 8]
- 398 - Change from baseline in sleep symptoms to last treatment [ Time Frame: Baseline, Week  
399 4]
- 400 - Change from baseline in sleep symptoms to Follow-up [ Time Frame: Baseline, Week 8]
- 401 - Change from baseline in Psychological and Physical Pain to last treatment  
402 [ Time Frame: Baseline, Week 4]
- 403 - Change from baseline in Psychological and Physical Pain to Follow-up  
404 [ Time Frame: Baseline, Week 8]

- 405       - Experiential questionnaires administered at every session immediately following infusion
- 406       - Subjective experiences of patients undergoing ketamine therapy assessed by semi-
- 407       structured interviews and audio recording [ Time Frame: Week 5 to 6]

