## **6. Study intervention and control groups**

The ketamine treatment procedure received by both the intervention and control groups will consist of six infusions given over four weeks. During the first two weeks, infusions will be given bi-weekly (on Mondays and Wednesdays) and weekly during the last two weeks (on Wednesdays). The patients will receive their infusions in a quiet room, in a semi-reclined position on a hospital bed or medical recliner at an angle of approximately 45 degrees. A vein will be cannulated and 0.5mg/kg of ketamine will be diluted in 250mL of normal saline by the treating team's nurse, according to clinical information (i.e. weight, height and BMI) and verified by one other member of the treating team before being administered continuously during 40-minute infusions. In patients with a BMI greater than 30, ketamine doses will be calculated based on the upper-limit BMI of 30, given that greater hemodynamic changes with a body mass index of 30 and above have been observed.

After cannulation and setup of the infusion equipment, patients will be left alone for ten minutes in order to allow an accurate measurement of baseline blood pressure. For these ten minutes, they will be asked to remain in the same semi-reclined position, in silence and without use of electronic devices such as cell phones. Clinicians will then return to the room and measure blood pressure in triplicate before beginning the infusion. The ketamine infusions will be given in the presence of the nurse and a physician with ongoing assessments of patients' physiological and mental status during the infusion. All patients will be offered blindfolds for the duration of the infusions.

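### Section 8.4 leaves the week-4 and week-8 music-control comparisons to a latent growth curve with no stated shape, time coding or arm contrast; fitted as a straight line, it would miss a benefit that is gone by week 8

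*Supplement*

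**What the plan says.** Section 2.2 sets a between-arm question: "we aim to assess if music can modulate diastolic blood pressure and clinical response to repetitive sub-anesthetic IV infusions" in depression, anxiety, suicidality, sleep and pain. Section 4.4 gives the arm sizes: "Eligible patients will be 1:1 randomized to the music-intervention (intervention, n=15) or usual care (control, n=15) groups".

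Section 5.2 lists the change to the last treatment and the change to follow-up as separate outcomes for each symptom domain, for example "Change from baseline in mood symptoms to Follow-up [ Time Frame: Baseline, Week 8". Sections 7.1.3 to 7.1.6 repeat this split scale by scale. Section 3 gives the measurement occasions: "Secondary outcomes will be measured at baseline and at each treatment session, as well as at 8-week follow-up".

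The analysis in Section 8.4 is one sentence. Its targets are "The change from baseline to the end of the treatment month and to the 8-week follow-up end"-point, and its methods follow: "point will be analyzed using traditional end-point analysis (paired T-test) and latent growth curve" analysis. The section does not say whether the curve is linear, quadratic, piecewise or free-form, how time is scaled, or which parameter tests music. Section 8.3, on the primary outcome, does state the link, working correlation, variance estimator and missing-data method.

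**The concern.** A paired t-test compares a patient with himself or herself. It shows whether scores moved within an arm, which ketamine alone may bring about in both arms. The growth curve is therefore the only method named for these outcomes that can compare music with control, and its music parameter is undefined.

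The usual first choice is a straight line, whose parameters are an intercept and a slope. Neither is the week-4 or the week-8 difference. Section 1 says of ketamine: "These benefits typically appear rapidly in responders, within hours or days of initial treatment, though may not persist". If the difference between arms followed a similar course, rising early and then waning, a straight line could not follow it. The rise and the fall would offset each other in the slope.

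Two things are at stake. A real benefit at the end of treatment could be reported as no effect of music. And with the shape left open, the same data could show no effect or a clear one, depending on a choice made after they are seen. A linear latent growth model with arm already has about 14 parameters (2 growth means, 3 variances and covariances, 7 residual variances, 2 arm effects) for 30 patients, so the data give little help in choosing a shape.

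**Working it through.** Section 8.4 gives no figure to reproduce. The check asks what a straight line does to a difference between arms that rises and then fades.

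**Visit days.** Section 6 says "infusions will be given bi-weekly (on Mondays and Wednesdays) and weekly during the last two weeks (on Wednesdays"). Counting the first Monday as day 0 gives days 0, 2, 7, 9, 16 and 23, and week 8 is day 56. The mean is 113/7 = 16.14 and the sum of squares about it is 2230.9. Day 56 alone supplies (56 - 16.14)²/2230.9 = 71% of that sum.

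**Assumptions.** The documents give no effect size or SD for these outcomes. Assumed: a 5-point benefit at the last treatment, between-patient SD 5, slope SD 0.05 per day, residual SD 5, 15 per arm, two-sided 0.05.

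**Straight line, benefit gone by week 8.**
- Difference between arms: 5t/23 up to day 23, then 5(56 - t)/33. At the visits: 0, 0.43, 1.52, 1.96, 3.48, 5, 0.
- Least-squares slope: -0.248/2230.9 = -0.00011 points per day.
- SE of the slope difference: √(0.05² + 25/2230.9) × √(2/15) = 0.117 × 0.365 = 0.043.
- The ratio is practically zero, so power is about 5%, the alpha level.
- The fitted difference at day 23 is 1.8 points instead of 5.

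**Week-4 ANCOVA, same data.**
- Variances: 50 at baseline and 25 + 0.0025 × 529 + 25 = 51.3 at day 23; covariance 25.
- Residual variance: 51.3 - 625/50 = 38.8, SD 6.23.
- SE: 6.23 × 0.365 = 2.28. Ratio: 5/2.28 = 2.20. Power is about 56% (27 df).

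**Benefit that builds gradually and persists.** The slope is 199.0/2230.9 = 0.089 per day, the ratio 0.089/0.043 = 2.09, and power about 52%. The loss is small.

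**Early benefit.** Take 5 points from the second visit, halved by week 8.
- The slope is -18.9/2230.9 = -0.008 per day and its power about 5%.
- The arm effect on the fitted intercept is 4.1 points, with SE √(25 + 25 × (1/7 + 16.14²/2230.9)) × 0.365 = 2.05. The ratio is 1.98 and power about 48%.
- A piecewise line with a knot at day 23 gives a fitted baseline-to-day-23 change of only 2.9 of the 5 points (power about 25%), because it has to ramp up in a straight line. Its fitted level difference at day 23 overshoots, at 5.9. The answer depends on which contrast is read.

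**A second set of assumptions** (1 SD at the last treatment, correlation 0.5 between visits, as Section 8.1 assumes for blood pressure):

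| Build-up | Share left at week 8 | Slope power |
|---|---|---|
| Gradual | 0 / 25% / 50% / 100% | 5% / 12% / 35% / 88% |
| Fast | 0 / 25% / 50% / 100% | 17% / 6% / 9% / 57% |

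With fast build-up and nothing left, the slope has the wrong sign (-0.32 SD over 8 weeks). A between-arm change score at the last treatment has 75% power throughout. With gradual build-up and full waning, a piecewise line reaches about 88% and a quadratic about 87%.

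**The case against.** The strongest reply is that nothing in the plan says linear. Latent growth curves are a family, and the second set of assumptions shows piecewise and quadratic members beating the change score. The loss comes from a straight-line shape, not from growth modelling itself. This stands. A reader might infer that the sponsor plans a straight line, or that every growth curve would hide the benefit; the documents support neither.

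A reader might also infer that the protocol expects the music effect to fade. It does not. The sentence in Section 1 raises only a possibility, and it concerns ketamine's benefit, which both arms receive. No passage predicts the course of the difference between arms.

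The size also depends on the scenario. Full waning after a gradual rise falls almost exactly where the slope is zero. Coding time by session number instead of day raises slope power there from 5% to about 22%. In the early-benefit case, the intercept and slope tested together have about 38% power, so some signal survives. But an arm effect on the intercept is nominally a baseline difference, which is easily read as chance imbalance.

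Finally, a growth model can give model-implied differences at week 4 and week 8, and Section 8.4 does name those time points. The differences are only as good as the shape, however: 1.8 instead of 5 in the first case above. These are also secondary outcomes in a self-described pilot, which limits the consequences.

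**Conclusion.** The point holds as a gap in specification with a real cost under one plausible choice. Section 8.4 names no between-arm estimate at week 4 or week 8 and leaves the comparison to a growth curve whose shape, time coding and arm contrast are open.

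If that curve is a straight line in days and the music benefit is gone by week 8, the slope test has about 5% power where a week-4 ANCOVA has about 56%. If the benefit persists after a gradual build-up, the figures are close (52% against 56%). Better-chosen shapes reduce the loss but need the course to be guessed: a knot at the last treatment works well for a gradual rise and poorly, on the change contrast, for an early one.

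The percentages rest on assumed effect sizes and SDs and on visit days inferred from the weekly schedule. The direction does not depend on the exact days: under the second set of assumptions, moving the last treatment to day 28 leaves slope power at 5% to 13% with full waning. The primary blood pressure analysis is not affected. The wording should be changed before the secondary data are analysed.

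**What to change.** Make the main longitudinal analysis of the symptom outcomes a repeated-measures mixed model. Treat visit as a category (pre-infusion 2 to 6 and week 8), with terms for arm, arm-by-visit and baseline score, fitted by REML with Kenward-Roger degrees of freedom. State the covariance structure and a simpler fallback in advance, since an unstructured matrix for six visits has 6 × 7/2 = 21 parameters for 30 patients. Report the music-control difference with its confidence interval at week 4 and at week 8. This assumes no shape for the course and estimates the two time points that Section 5.2 lists.

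The paired t-test can stay as a description of change within each arm, labelled as such. Any growth curve should be exploratory, with its shape, time coding and arm contrast fixed in advance, for example a knot at the last treatment.

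The cost is a few sentences of analysis text and the loss of a single-number summary of the trajectory. No new visits, data or patients are needed.

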**PROTOCOL SUMMARY**

|                                   |                                                                                                                                                                                                                                                                                                                                                                                                                                                                                                                                                                             |
|-----------------------------------|-----------------------------------------------------------------------------------------------------------------------------------------------------------------------------------------------------------------------------------------------------------------------------------------------------------------------------------------------------------------------------------------------------------------------------------------------------------------------------------------------------------------------------------------------------------------------------|
| Title                      | Music as an Intervention to Improve Hemodynamic Tolerability of Ketamine in Depression                                                                                                                                                                                                                                                                                                                                                                                                                                                                               |
| Objectives                 | 
Primary: To assess whether music improves hemodynamic tolerability by mitigating systolic blood pressure elevation during a course of intravenous ketamine for treatment-resistant depression
 
Secondary: To assess whether music improves mood, anxiety, suicidality, and psychological/physical pain during a course of intravenous ketamine for treatment-resistant depression.
 
Exploratory: To explore both quantitatively and qualitatively how various aspects of the treatment experience, with and without music, influence secondary outcomes.
 |

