| Study design               | Prospective, two-center, single-blinded, randomized controlled trial with a parallel two-arm group.                                                                                                                                                                                                                                                                                                                                                                                                                                                                         |
| Primary outcome measure    | Changes in Systolic Blood Pressure from 0 to 40 minutes of each infusion                                                                                                                                                                                                                                                                                                                                                                                                                                                                                                    |
| Secondary outcome measures | Changes in measures of depression, anxiety, sleep, psychological and physical pain                                                                                                                                                                                                                                                                                                                                                                                                                                                                                          |
| Population                 | 30 patients with Treatment resistant depression recruited and randomized into curated music (n=15) or                                                                                                                                                                                                                                                                                                                                                                                                                                                                       |

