## **8.2. General considerations**

The analyses will be performed based on the intention- to-treat principle. Baseline variables by treatment groups will be characterized in a summary table. Between-group differences at baseline will be inspected and judged according to clinical relevance. The assessment of compliance with the intervention and safety/tolerability will be summarized for both groups. Adverse events, if any, will be reported by treatment group.

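### Section 8.4 names no music versus no-music comparison for the secondary clinical outcomes: the paired t-test measures change on ketamine, and the growth curve is not said to include arm

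*Supplement*

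**What the plan says.** The secondary objective in the Protocol Summary is "To assess whether music improves mood, anxiety, suicidality, and psychological/physical pain during a course of intravenous ketamine for treatment-resistant depression". Section 2.2 says the same more broadly: "As secondary objectives, we aim to assess if music can modulate diastolic blood pressure and clinical response to repetitive" ketamine infusions, across depression, anxiety, suicidality, sleep and pain. The design is a "randomized controlled trial with a parallel two-arm group", and section 4.4 fixes the allocation: "Eligible patients will be 1:1 randomized to the music-intervention (intervention, n=15) or usual care (control, n=15) groups". Section 6 gives both arms the same ketamine course.

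Section 5.2 defines the clinical secondary outcomes as within-patient changes, for example "Change from baseline in mood symptoms to last treatment", without naming the groups. Diastolic pressure is the exception: its change from 0 to 40 minutes is defined between arms. The same list includes experiential questionnaires given only after infusions.

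The analysis of all this is one sentence in section 8.4. Change to the end of the treatment month and to the 8-week follow-up "will be analyzed using traditional end-point analysis (paired T-test) and latent growth curve" analysis. It gives no arm term, contrast, covariate or effect measure. Section 8.3 does specify an estimated difference between arms by GEE, but only for the primary outcome. Section 8.2 adds that "The analyses will be performed based on the intention- to-treat principle", together with a baseline table and summaries of compliance and safety by group.

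**The concern.** The objectives concern the effect of music. Each patient is in one arm only, so nothing is paired across arms. A paired t-test therefore compares each patient's later score with the same patient's baseline. Run on everyone, it tests whether patients given ketamine changed. Run in each arm, it asks that question twice and never tests the difference.

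Two misreadings follow. If patients improve strongly, both arms are significant and the result says nothing about music. If improvement is moderate, one arm can pass 0.05 and the other miss it by chance, and a reader may take that as a music effect. Section 8.1 says the pilot is meant to supply data for planning a confirmatory trial. That requires an estimated arm difference with its uncertainty, which within-arm p-values do not give.

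**Working it through.** The plan states no power, effect size or expected change for the secondary outcomes, so there is no figure of its own to reproduce. The check shows how the named test behaves when music does nothing.

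**Inputs from the documents.** 15 patients per arm (section 4.4); ketamine in both arms (section 6).

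**Assumptions.** Two-sided alpha 0.05, which section 8.1 states for the primary outcome only. A standardised within-patient change dz (mean change divided by the SD of change), equal in both arms, so the true music effect is zero. Separate paired tests in each arm, which section 8.4 does not state. Complete data.

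**Step 1, rejection probability in one arm.** The paired t statistic has n − 1 = 14 degrees of freedom and noncentrality dz × √15 = 3.873 × dz. The two-sided rejection probability p comes from the noncentral t distribution.

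**Step 2, probability that the arms disagree.** The arms are independent, so P(exactly one significant) = 2p(1 − p).

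| Assumed dz | Noncentrality | p, one arm of 15 | 2p(1 − p) |
|---|---|---|---|
| 0.5 | 1.94 | 0.438 | 2 × 0.438 × 0.562 = 0.49 |
| 0.7 | 2.71 | 0.713 | 2 × 0.713 × 0.287 = 0.41 |
| 1.0 | 3.87 | 0.949 | 2 × 0.949 × 0.051 = 0.10 |
| 1.5 | 5.81 | 1.000 | about 0 |

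Half of each disagreement favours music. At dz 0.5, music alone is significant in 0.438 × 0.562 = 25% of trials despite having no effect.

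**Step 3, one paired test on all 30 patients.** If section 8.4 means this instead, the test is significant in 75% of trials at dz 0.5, 98% at 0.75 and over 99% at 1.0, again with no music effect. It detects the common change.

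**Step 4, a direct comparison.** A two-sample t-test on change scores, 15 v 15, keeps a 5% false-positive rate whatever the common change. In 40,000 simulated trials it rejected in 4.9% at both dz 0.5 and dz 1.0. The same simulation gave disagreement between arms of 49% and 10%, matching the table.

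**Step 5, what the direct comparison can detect.** Its power is 26% for an arm difference of 0.5 SD of change, 56% for 0.8 and 75% for 1.0. The difference detectable with 80% power is 1.06 SD (1.10 with 14 per arm). Adjusting for baseline may improve this, by an amount that depends on a correlation the documents do not give. At this size the confidence interval will be more informative than the p-value.

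**The case against.** The strongest reply is that section 8.4 names two analyses. A growth curve with arm as a predictor of slope is a between-arm analysis, and sections 2.2 and 5.2 show that a comparison is intended. This limits the point: a reader might infer that the plan has no route to its secondary objectives, and the text does not support that. It supports only that no between-arm comparison is specified. The reply does not rescue the paired test, and it leaves the only possible comparison to a model whose arm term and contrast are unstated.

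Two other inferences also go too far. One is that the paired test breaks the intention-to-treat principle by dropping patients without both readings. Section 8.4 gives no missing-data rule, imputation could come first, and a likelihood-based growth curve can use incomplete records. All that can be said is that missing-data handling for these outcomes is unstated. The other is that a growth curve is too fragile for 30 patients. Nothing in the documents shows this, and a repeated-measures model with an unrestricted covariance matrix is also demanding at that size.

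It is fair, too, that the percentages rest on assumed changes. The function 2p(1 − p) cannot exceed 50%, so 49% is close to the worst case, and disagreement fades as the common change grows. At large changes the other failure takes over, with both arms significant whatever music does.

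Finally, this is a pilot, these are secondary outcomes, and the primary outcome already has a between-arm estimate. That makes the choice between ANCOVA, a repeated-measures model and an arm-on-slope term largely a matter of preference. It does not remove the need to state one of them.

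**Conclusion.** The point holds in this form: section 8.4 specifies no comparison of music with no music for the secondary clinical outcomes. Its named end-point test addresses a different question from the objectives, and its growth curve is not stated to include arm. No other section fills the gap, because the GEE of section 8.3 is confined to the primary outcome.

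That conclusion comes from the text and needs no numerical assumption. The size of the consequence does depend on assumptions. With zero music effect, equal standardised changes and separate tests in complete arms of 15, the arms disagree in 49%, 41% and 10% of trials at changes of 0.5, 0.7 and 1.0. At 1.5 both are significant almost always. In no part of this range do paired tests show a music effect.

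The wording of section 8.4 also leaves two kinds of secondary outcome uncovered: diastolic pressure, which is a change within each infusion, and the experiential questionnaires, which have no pre-treatment score. The arm comparison should be written into the plan before the data are analysed.

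**What to change.** Rewrite section 8.4 along these lines.

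- **Scales with a baseline (mood, anxiety, suicidality, sleep, pain).** Make the inferential analysis a baseline-adjusted difference between arms with 95% CI at Week 4 and at Week 8. Either ANCOVA at each time or a repeated-measures model with arm-by-visit contrasts is enough; if the latter, name the covariance structure.
- **Growth curve.** State that arm is a predictor of slope and that this term is the comparison of interest.
- **Paired changes within arms.** Report them as description only, with no inference about music drawn from them.
- **Diastolic pressure, 0 to 40 minutes.** Use the between-arm GEE of section 8.3.
- **Post-infusion experiential questionnaires.** Compare those completed in both arms between arms, without a baseline term.
- **Missing data.** Add a sentence on how missing secondary outcomes are handled, since the weighting in section 8.3 covers only the primary outcome.

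The cost is a short rewrite of one section. Sections 3 and 7.3 already schedule the pre-infusion, post-infusion and follow-up assessments required, so no data collection changes.
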